#### Procedure for unblinding if needed {17b}

Not applicable as participants, clinical coaches, and parent coaches will not be blinded to condition.

### Data collection and management

#### Plans for assessment and collection of outcomes {18a}

Data will be collected via self-report measures, Fitbit devices (Fitbit Inspire 2), online video assessment, the use of back-end app data via Firebase and Google Analytics, and forum content.

The primary outcome of change in depression symptoms will be assessed using the Patient Health Questionnaire (PHQ-9) [57]. Secondary outcomes include changes in *anxiety symptoms*, assessed using the Generalized Anxiety Disorder 7-Item Scale (GAD-7) [59], *family relationship quality*, assessed with the Parental Assistance with Child Emotion Regulation (PACER) [61], the Social Support Effectiveness Questionnaire (SSEQ) [64], and the Couple Satisfaction Index (CSI) [65], *parenting*, assessed using the Parenting Stress Index (PSI) [60], the Parenting Scale [62], and the Parenting Young Children (PARYC) measure [63], and *maternal functioning* assessed using a variety of validated self-report questionnaires for mental health symptoms, including the Patient-Reported Outcomes Measurement Information System (PROMIS) Anger Subscale [66], the Self-Compassion Scale Short-Form [67], the PROMIS Sleep Disturbance Scale [69], the Depression Symptom Index Suicidality Subscale [70], the Single Item Self-Esteem Scale [68], the Alcohol Use Disorder Identification Test (AUDIT) [71], and the Cannabis Use Disorder Identification Test – Revised (CUDIT-R) [72]. There will also be additional measures of suicidality and self-harm, depression persistence, recent stressful experiences, mental health medication and service use, and an additional measure of substance use, which have been developed for the BEAM project. *Child Functioning* will be measured using validated questionnaires for child mental health and behavior, including the Preschool Pediatric Symptom Checklist [73] and a subset of questions from the Early Child Behavior Questionnaire [74]. Additional measures of screen time and child health, which have been developed for the BEAM program, will also be used.

Online video assessments will be conducted to measure exploratory outcomes of parent-child relationship quality, child emotional reactivity, maternal sensitivity (e.g., Maternal Q-sort), and sensitive parenting (e.g., child-directed speech). Online video assessments will take place over Zoom with mother-child dyads. Assessors will be undergraduate psychology students who have undergone extensive training in conducting Zoom assessments with families. Training involves watching practice videos and practicing the assessments with pilot families under the supervision of psychology graduate students as well as registered psychologists on the research team. Exploratory outcomes will also include physiological measures obtained through the use of Fitbit devices (Fitbit Inspire 2), including heart rate, sleep quality and duration, and physical activity. Feasibility of the BEAM program will be assessed using the mHealth App Usability Questionnaire self-report questionnaire (MAUQ) [76] and other questionnaires developed for the BEAM program. Firebase and Google Analytics will be used to track program engagement and adherence and the content of posts and comments within the forum will be used for program improvement purposes.

Additional self-report questions will be administered to assess demographic and socioeconomic characteristics and personality will be assessed using the Big Five Inventory-10 (BFI-10) measure, which will be adapted from the original questionnaire [77].

#### Plans to promote participant retention and complete follow-up {18b}

Three scheduled study-related reminders will be sent to participants each week through the BEAM app and participants will receive one weekly email reminder which will include information for group telehealth sessions. Eligible participants will receive up to $150 Canadian (CAD) compensation for participating for the entire duration of the study. Participants will receive an honorarium of $20 CAD for completing the pre-assessment questionnaires, $30 CAD for completing the post-intervention assessment, $20 CAD for completing the follow-up assessment, and $30 CAD if they complete all weekly surveys ($3 CAD per week) and will receive another $50 CAD if they choose to mail back the Fitbit used for data collection during the study. Furthermore, the clinical research team will have weekly meetings to monitor the adherence and retention of participants. For instance, group attendance will be discussed and additional email check-ins with participants will be performed when advised by the registered psychologists on the team.

#### Data management {19}

REDCap is managed by The George and Fay Yee Centre for Healthcare Innovation, which is a hired consultant on the proposed project and will support secure data collection and management. RCT data will be stored on a secure server in accordance with the University of Calgary’s Data Retention Policy and the University of Manitoba’s PHIA policies. Once data is downloaded, all identifying information will be removed, which aligns with the University of Manitoba’s REDCap policies. All patient health information and identifiable information will be kept for up to 5 years. Birth dates will be converted into age in months, and birthdate information will then be destroyed. For the storage of Zoom assessment data, raw video data will be destroyed no later than 5 years after collection. Once videos have been coded by trained observers, the original file and all copies will be deleted. Measures to promote the quality of data entry will include range checks for all data values entered and having three research assistants review and ensure correct data entry in REDCap.

#### Confidentiality {27}

The BEAM program will occur on a secure online platform and participant confidentiality will be protected throughout all phases of the study in accordance with University of Manitoba and University of Calgary ethics guidelines. Only the research team will have access to study data and only de-identified data will be transmitted to coinvestigators. All those with access to data are trained in the University of Manitoba’s and University of Calgary’s ethics and data safety protocols, have completed additional training on the Public Health Information Act, and have taken an oath of confidentiality.

Assessment data will be stored securely on REDCap or on password-protected University of Manitoba secure data servers. Any documents including identifying information will be password-protected and stored on University of Manitoba secure data servers. All questionnaire data will be exclusively linked to de-identified participant ID numbers once it has been downloaded from REDCap. Qualitative data from forums will be anonymous and not linked to any identifying information on the platform. Fitbit data will be stored in Fitabase’s high-security cloud-based database [75] until the trial is complete, at which point it will be downloaded and deleted.

Precautions will be taken to manage any risks to confidentiality of personal data on the forum. These precautions include a Risk Management Protocol, Data Management Protocol, participant agreed upon Terms of Use, and the ability for program coaches to remove any posts that violate the terms or use and to email any participants should there be concerns.

To protect participant privacy and confidentiality and to ensure that no health information is shared on the forum, all participants will be required to agree to the community guidelines including the Rules and Terms of Use of the online forum and will agree not to disclose any identifying information to other participants. Security measures include monitoring of the forums by the study team, and the ability for other participants to anonymously flag posts for review. A risk management protocol will be put in place by clinician leads in each province to manage any potential crisis-related mental health or child safety needs.

During the weekly telehealth sessions, participant anonymity cannot be guaranteed. The telehealth sessions will be hosted on a secure Zoom Healthcare account and will be password-protected. The clinical coaches will outline the limitations of confidentiality and anonymity at the beginning of the first telehealth session. Telehealth meetings will not be recorded or included in any assessment; however, attendance will be tracked. The Jane app will also be used as the clinical record management tool (i.e., to track attendance to telehealth sessions and make session notes).

Participants will become familiar with the limitations to confidentiality and of the measures that will be taken to protect the confidentiality during the informed consent process before beginning in the study.

#### Plans for collection, laboratory evaluation, and storage of biological specimens for genetic or molecular analysis in this trial/future use {33}

Not applicable, no biological specimens will be collected.

## Statistical methods

### Statistical methods for primary and secondary outcomes {20a}

Between-group differences in primary and secondary outcome variables, as well as quantitative exploratory outcome variables (observational and Fitbit data), will be analyzed using linear mixed models. Models will test both a linear and quadratic time coefficient, where quadratic time coefficients will be removed from final models if not significant. An *α* of 0.05 will be used to determine statistical significance. Effect sizes of 0.20, 0.50, and 0.80 will be interpreted as indicating small, medium, and large effects, respectively [80]. Standardized effect sizes for linear mixed models will be derived based on existing recommendations for linear mixed models [80, 81]. The research team will also investigate if there is baseline moderation by symptom severity to examine whether the BEAM intervention is more effective than the control group for participants who have higher symptom levels at pre-intervention (e.g., depression, anxiety, insomnia).

Exploratory qualitative data will be analyzed thematically [82]. First, two analysts will concurrently, but independently read the transcripts for surface descriptive content, and organize like-with-like ideas. Second, transcripts will be re-read for latent meaning to better understand participants’ meaning, including looking for contradictory or confirmatory statements. Each analyst will independently generate and systematically apply themes across all transcripts. Semantic validity checks will ensure different words and phrases within a category have similar meanings [82]. To further enhance rigor, constructs will be deemed saturated (akin to statistical significance in quantitative work) when no new or additional constructs are identified, consensus is reached on all overarching themes, and no alternative explanations were found with subsequent interviews [82].

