Addressing the intergenerational impact of perinatal mental health problems requires innovative program design methods to simultaneously treat maternal mental illness and promote parenting abilities [25, 30]. In collaboration with a parent advisory board, we have developed the Building Emotion Awareness and Mental Health (BEAM) program to respond to the needs of mothers managing depression, anxiety, and parenting stress. The BEAM program provides app-based psychoeducation and group telehealth sessions with a mental health professional while prioritizing peer support as a central component of the program. Following the ORBIT model for developing behavioral therapies to treat or prevent chronic diseases and enhance health-promoting behaviors [41, 42], our research team previously conducted a phase II (preliminary testing) pilot trial of the BEAM program for mothers of children aged 18 to 36 months of age who self-reported moderate-to-severe symptoms of depression and or anxiety. The results revealed interaction effects with greater reductions in overall mental health problems among participants in the BEAM program compared to the control group [43]. Findings were used to determine the clinical impact of the program and inform improvements. The current study represents the phase III (efficacy testing) randomized controlled trial (RCT) of the BEAM program.

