##### Coaching

Parent coaches will be mothers who have recently completed another research group-based intervention for their own mental health needs and who are interested in being a part of the community to promote the mental wellness of mothers. Parent coaches will help to conduct Zoom orientation meetings (detailed below) with participants prior to the program start date, will engage with participants on the forum, and co-facilitate weekly telehealth sessions.

Clinical coaches will be clinical trainees or registered mental health professionals. Clinical coaches will monitor the forums, facilitate weekly group telehealth sessions, and manage participant contact by email as needed. Clinical coaches will also participate in weekly consultation meetings with clinical supervisors (i.e., registered psychologists).

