#### Sample size {14}

Based on the findings from a meta-analysis, digital interventions for depression that include a human therapeutic guidance component (as is the case with the BEAM program group therapy sessions) have a moderate effect on depression (*g* = .63) [78]. Thus, an a priori, one-tailed, two-group power analysis was conducted using a moderate effect size (*d* = .5) using the G* Power 3 software [79]. The power analysis indicated that we would need 51 participants per group to reach 80% power (*α* = .05) to detect a clinically significant change in depression. To account for anticipated attrition of approximately 25%, a total sample of 140 with 70 in each group (intervention and control) will be the target for recruitment.

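### BEAM is delivered in telehealth groups and TAU is not, but the sample size allows nothing for clustering and the stated model names no group or timeslot term

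*Protocol article*

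**What the plan says.** **Delivery.** The Intervention description {11a} and the section on social support and community connection have BEAM participants attend weekly group sessions over video. Under Coaching, "Clinical coaches will monitor the forums, facilitate weekly group telehealth sessions, and manage participant contact by email as needed", and parent coaches co-facilitate. The Background and rationale {6a} describes the programme as combining app content and group sessions "while prioritizing peer support as a central component of the program". The section on comparators {6b} says that TAU participants simply continue their standard care.

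**Allocation.** Sequence generation {16a} stratifies the 1:1 randomization by the telehealth timeslot that each participant could attend.

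**Sample size {14}.** The protocol states that "an a priori, one-tailed, two-group power analysis was conducted using a moderate effect size" of d = 0.5, and that "we would need 51 participants per group to reach 80% power". The only adjustment is for dropout: "To account for anticipated attrition of approximately 25%, a total sample of 140 with 70 in each group".

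**Analysis {20a}.** Comparisons of the two arms "in primary and secondary outcome variables, as well as quantitative exploratory outcome variables (observational and Fitbit data), will be analyzed using linear mixed models". The section gives the time terms, the rule for dropping the quadratic term, the effect-size conventions and an alpha "of 0.05 will be used to determine statistical significance". It states no random-effects structure and mentions no telehealth group, coach or timeslot.

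The number of groups, their size and an ICC appear nowhere.

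**The concern.** Participants who share a coach and a set of peers for 10 weeks may end with correlated outcomes, and the programme intends that kind of mutual influence. This can arise in the BEAM arm only. The variance of the BEAM mean is then larger than for the same number of unrelated people. A model that accounts for repeated measures on a person, but not for the group, misses this.

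Two things are at stake. The first is the stated 80% power, which was computed as if there were no clustering. The second, depending on how the model is finally specified, is the p-value and confidence interval for PHQ-9, in a trial that the protocol presents as efficacy testing.

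**Working it through.** **1. Reproduce the planned figure.** Inputs from Sample size {14}: d = 0.5, one-tailed alpha 0.05, power 80%, two groups. The exact noncentral t calculation gives 79.9% power at 50 per group and 80.6% at 51, so the answer is 51, as stated. This is the figure for independent observations, with design effect 1. Dropout: 51 / 0.75 = 68 per arm, or 136 in total, which the protocol rounds up to 140.

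**2. Room for clustering.** 140 × 0.75 = 105 expected completers against 102 needed, a margin of 105/102 = 1.029.

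With m analysed members per group, the design effect in the BEAM arm is DE = 1 + (m − 1) × ICC. TAU keeps a factor of 1. Relative to independence, the variance of the difference is multiplied by R = (1 + DE)/2.

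Setting R = 1.029 gives (m − 1) × ICC = 0.059. The margin is therefore used up at an ICC of about 0.015 for m = 5, 0.007 for m = 10 and 0.004 for m = 15.

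**3. Consequence if no group term is fitted.** Assumptions, since the documents give no values: m from 5 to 15, ICC from 0.01 to 0.10, equal group sizes, all of the ICC induced by the group, 51 analysed per arm, and one post-baseline comparison.

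- True two-sided size = 2 × [1 − Φ(1.96/√R)]
- One-tailed power with the correct standard error = Φ(0.5/√((1 + DE)/51) − 1.645)

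Example, m = 10 and ICC 0.05: DE = 1 + 9 × 0.05 = 1.45 and R = 1.225. Size = 2 × [1 − Φ(1.96/1.107)] = 7.7%. Power = Φ(0.5/0.219 − 1.645) = 73.8%.

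| Group size | ICC | DE | True two-sided size | One-tailed power, correct SE |
|---|---|---|---|---|
| 5 | 0.01 | 1.04 | 5.2% | 80.4% |
| 10 | 0.01 | 1.09 | 5.5% | 79.5% |
| 15 | 0.01 | 1.14 | 5.8% | 78.7% |
| 5 | 0.05 | 1.20 | 6.2% | 77.7% |
| 10 | 0.05 | 1.45 | 7.7% | 73.8% |
| 15 | 0.05 | 1.70 | 9.2% | 70.1% |
| 5 | 0.10 | 1.40 | 7.4% | 74.5% |
| 10 | 0.10 | 1.90 | 10.4% | 67.4% |
| 15 | 0.10 | 2.40 | 13.3% | 61.5% |

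The same normal approximation gives 5.0% and 81.1% with no clustering. Simulated t tests that ignore the groups (5 groups of 10, 20,000 runs) give 7.4% at ICC 0.05, 10.3% at ICC 0.10 and about 5% at ICC 0.

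**4. Separate the timeslot from the group.** Timeslot is a randomization stratum, so a tendency for people in one slot to resemble each other is shared by both arms and cancels from the difference. Write the BEAM ICC as a + b, where a comes from timeslot and b from the group. With balanced strata, R = [m·b + (1 − a − b) + (1 − a)]/2. For m = 10 and a + b = 0.05:

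- all group (b = 0.05): R = 1.225, size 7.7%
- split equally: R = (0.25 + 0.95 + 0.975)/2 = 1.0875, size about 6.0%
- all timeslot (a = 0.05): R = (0.95 + 0.95)/2 = 0.95, size about 4.4%, slightly conservative

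**The case against.** The strongest reply is that the protocol does not say the mixed model treats BEAM participants as independent. It names a model class and time terms and leaves every random effect unstated, even the one for participant. A linear mixed model can carry a group effect, and an analysis plan not shown here may specify one. This stands. A reader might infer from the protocol that type I error will exceed 5%, but the text does not support that. Inflation needs both an omitted group term and a group-induced ICC above 0, and neither is documented. At the low end of the range it is negligible.

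Second, not all within-slot similarity does harm. Stratification balances whatever comes from timeslot choice, as step 4 shows. This also stands, so the sizes in step 3 are upper figures for a given total ICC.

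Third, the forum is open to the whole BEAM arm and the videos are watched individually, so the emphasis on peer support does not by itself show correlation within telehealth groups. Nor does the protocol say that group membership is fixed. This is fair. The case for clustering rests on the shared coach and weekly sessions, and its strength is unknown.

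Fourth, a reader might charge to clustering the whole fall in power to about 63% two-sided (51 per arm, groups of 10, ICC 0.05). Most of it is not due to clustering. Moving from a one-tailed to a two-tailed test takes power from 81% to 71% with no clustering at all. That is a separate issue and is not counted here.

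None of these replies touches the sample size, where independence is what the stated figure implies.

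**Conclusion.** The point holds in conditional form. It is firm that the design is partially nested, that 51 per group is exactly the independent-observations answer, and that the recruitment target leaves almost no margin for a design effect. It is also firm that the analysis section, which goes as far as a rule for the quadratic term, names no group or timeslot term.

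The effect on inference is conditional. If no group term is fitted and the ICC is wholly group-induced, two-sided size runs from 5.2% to 13.3% over groups of 5 to 15 and ICCs of 0.01 to 0.10. One-tailed power at 51 per arm, with the correct standard error, runs from about 80% down to 61.5%. These ranges rest on assumed group sizes and ICCs and on a single-timepoint approximation to the repeated-measures model. The analysts are not blinded to condition {17a}, so the treatment of groups is better settled in writing before the data are analysed.

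**What to change.** **Statistical methods {20a}.** Include the randomization timeslot as a covariate. Add a random effect for telehealth group in the BEAM arm only, acting at the post-baseline assessments, with TAU participants ungrouped. Use Satterthwaite or Kenward-Roger degrees of freedom. If an analysis plan already does this, a sentence saying so is enough.

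**Sample size {14}.** State the number and size of the groups and a range of ICCs, and restate power for the planned 140 under that range. The Trial status section reports that recruitment has finished, so this is a matter of disclosure and does not call for enrolling more.

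**Cost.** Wording and analysis code. Timeslot is already recorded for randomization {16a} and session attendance is tracked {27}. The drawbacks are wider intervals, an imprecisely estimated group variance if there are only a few groups, and a less favourable stated power.

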### Trial design {8}

A two-armed, parallel-design randomized controlled superiority trial with repeated measures will be used to evaluate the efficacy of the 10-week app-based BEAM intervention for mental health and parenting outcomes in parents of children aged 18–36 months (at study enrollment) compared to the treatment as usual (TAU) control group. Participants will be randomly allocated, using central randomization stratified based on telehealth session availability, in a 1:1 ratio to the BEAM program or TAU. Primary (depression) and secondary (anxiety, family relationship quality, parenting stress and behaviors, and maternal and child socioemotional functioning) outcomes will be assessed during the enrollment period (pre-test, T1), after the last week of the BEAM intervention (post-test, T2), and at follow-up (T3). Exploratory outcomes (parent-child relationship quality, maternal sensitivity, child emotional reactivity, and physiological indices) will be assessed at T1 and T2.

This trial adheres to the Standard Protocol Items: Recommendations for Intervention Trials (SPIRIT) guidelines [82] and was registered with ClinicalTrials.gov (NCT05306626). All procedures will be performed in accordance with the Research Ethics Board at the University of Manitoba, Fort Garry campus and the 1964 Helsinki Declaration and its later amendments. All participants will provide informed consent prior to enrollment in the study.

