### Outcomes {12}

#### Primary outcomes

The primary outcome is mean change in depression symptoms from pre- to post-intervention and from pre-intervention to follow-up, assessed using the Patient Health Questionnaire-9 (PHQ-9) [57], a self-report questionnaire that measures depression severity. Participant depression symptoms will be measured during eligibility screening pre-intervention (T1), immediately after intervention (T2), and at a 6-month follow-up (T3). The PHQ-9 includes nine items, asking participants to report over the past week how often they have been bothered by certain problems. Participants respond to each item using a 4-point Likert scale ranging from 0 (*not at all*) to 3 (*nearly every day*). Possible scores range from 0 to 27, with higher scores indicating more severe depression symptoms. Participant scores are summed, and a cutoff score of ≥ 10 will be used to identify participants who present with clinically concerning symptoms of depression [57]. The PHQ-9 cutoff score of 10 has been shown to demonstrate high sensitivity and specificity in detecting depression in a perinatal population [58].

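### Dropping a non-significant quadratic time term forces the T1–T2 group difference onto a straight line and can materially understate an effect that is largely complete by T2

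*Protocol article*

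**What the plan says.** Under Primary outcomes, the protocol article states: "The primary outcome is mean change in depression symptoms from pre- to post-intervention and from pre-intervention to follow-up". The PHQ-9 is taken at three visits: T1, T2 and T3.

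Under Statistical methods for primary and secondary outcomes {20a}, the primary, secondary and quantitative exploratory outcomes "will be analyzed using linear mixed models". The time terms are governed by this rule: "Models will test both a linear and quadratic time coefficient, where quadratic time coefficients will be removed from final models if not significant". On the significance level, the section says only that an alpha "of 0.05 will be used to determine statistical significance".

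The section does not say whether the quadratic term under test is the overall time curve or its interaction with group. The rule also covers outcomes with only two visits. Trial design {8} states: "Exploratory outcomes (parent-child relationship quality, maternal sensitivity, child emotional reactivity, and physiological indices) will be assessed at T1 and T2".

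**The concern.** The primary outcome asks two separate questions: how far the arms differ in change by the end of the programme, and how far by follow-up. With three visits, linear plus quadratic time by group gives each question its own answer. Without the group-by-quadratic term, one slope answers both, and the T1–T2 difference becomes a fixed fraction of that slope.

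The article places T2 straight after a 10-week programme. An effect that arises during the programme and then holds is therefore a natural pattern, and a straight line fits it badly. The test that decides whether the line is used has low power at this sample size, so a non-significant result says little about whether the line is adequate. At stake are the size and the interval of the reported T1–T2 effect. The rule is also applied outcome by outcome, so some T1–T2 effects would come from a line and others from a curve.

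**Working it through.** **Plan's own figure.** Sample size {14} describes a "one-tailed, two-group power analysis was conducted using a moderate effect size" of d = 0.5, with alpha 0.05 and 80% power. A one-sided two-sample t test gives 51 per group (power 0.806), as stated. After about 25% attrition, 70 × 0.75 = 52.5 remain, so 52 per arm is used below.

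**Inputs.** From the article: T2 at weeks 12–16 and T3 at month 6 (taken as week 26), both from the Participant timeline. Assumed, because the article gives no figure: within-person correlation ρ of 0.3 to 0.7, equal at all pairs of visits; complete balanced data; arms free to differ at baseline; a two-sided 0.05 test on group-by-quadratic. True group difference in SD units: (0, -0.5, -0.5).

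**Step 1: the effect once the term is dropped.** Slope = Σ(t − t̄)d / Σ(t − t̄)².
- T2 at week 12: t̄ = 12.67; slope = -6.333 / 338.67 = -0.0187 per week. T1–T2 = 12 × -0.0187 = -0.224. T1–T3 = 26 × -0.0187 = -0.486.
- T2 at week 16: t̄ = 14; slope = -7 / 344 = -0.02035 per week. T1–T2 = -0.326. T1–T3 = -0.529.

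So T1–T2 is 35% to 55% too small, while T1–T3 stays close to -0.50.

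**Step 2: how often the term is dropped.** The quadratic contrast has weights (t3 − t2, −(t3 − t1), t2 − t1) and variance (2/n)(1 − ρ)Σw².
- Week 12, ρ = 0.5: weights (14, -26, 12); contrast 13 − 6 = 7; variance (2/52)(0.5)(1016) = 19.54; SE 4.42; z = 1.58; power 0.354; dropped in 65%.
- Week 12, ρ = 0.7: SE 3.42; z = 2.04; power 0.534; dropped in 47%.
- Week 16, ρ = 0.3: weights (10, -26, 16); contrast 13 − 8 = 5; SE 5.27; z = 0.95; power 0.158; dropped in 84%.

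**Step 3: the whole rule.** At week 12 and ρ = 0.5, the mean T1–T2 estimate is -0.223 when dropped and -0.682 when kept: 0.647 × -0.223 + 0.353 × -0.682 = -0.385. Simulation (40,000 trials per row, normal approximation) gives:

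| T2 week | ρ | Dropped | Mean T1–T2 (true -0.50) | 95% interval coverage |
|---|---|---|---|---|
| 12 | 0.3 | 73% | -0.37 | 44% |
| 12 | 0.5 | 65% | -0.39 | 42% |
| 12 | 0.7 | 47% | -0.43 | 52% |
| 16 | 0.3 | 84% | -0.39 | 78% |
| 16 | 0.5 | 80% | -0.40 | 73% |
| 16 | 0.7 | 69% | -0.42 | 65% |

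The mean T1–T3 estimate stays at about -0.49 to -0.52, with about 95% coverage.

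**Step 4: the reverse error.** With no effect at T2 and -0.5 at T3, the rule declares a T1–T2 effect in about 33% to 56% of trials, where a direct contrast does so in 5%.

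**Step 5: power.** With -0.5 at T2 fading to -0.25 at T3 (week 12, ρ = 0.5), the rule rejects for T1–T2 in 67% of trials against 72% for the direct contrast. Across the range the loss is about 3 to 6 points. Under the maintained effect the rule rejects more often (80% against 72%).

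**Step 6: spacing.** The abstract puts T3 three months after the intervention, the timeline at month 6, and Primary outcomes at a six-month follow-up. If T3 meant six months after the intervention (visits at weeks 0, 14 and 37), dropping the term gives T1–T2 = -0.170 and T1–T3 = -0.451.

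**The case against.** A reader might infer more than the documents support, and most of the case against those stronger readings stands.

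- *That the model estimates neither primary change.* It does when the group-by-quadratic term is kept: three visits then saturate the model, and both changes are exact combinations of coefficients. When the term is dropped, T1–T3 is still nearly unbiased under a maintained effect. The harm is confined to T1–T2 in the dropped case. How contrasts are extracted from a fitted model can be left to an analysis plan.
- *That the reported effect is simply halved.* The -0.22 is the value given that the term is dropped, with T2 at the early end of its window. Averaged over the rule the shortfall is about 14% to 26%. A truly linear effect loses nothing.
- *That power collapses.* In the fading case the slope test alone has only 22% power, but it applies only in the 38% of trials where the term is dropped.
- *That the rule chooses the estimand after the data are seen.* Primary outcomes fixes the target; the rule chooses the model used to reach it.
- *That exploratory results are spoiled.* A quadratic cannot be estimated from two visits, but linear time over two visits already is the T1–T2 contrast. The wording is untidy; no result is biased.

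The drop rates also depend on which term is tested. If it is the overall time curve, and usual care improves by 0.3 to 0.5 SD by T2 and holds (ρ = 0.5), the drop rate is about 6% to under 1%. With no change under usual care it is again 65%. The article does not settle this. None of these points defends the removal clause itself, which is a stated rule and not a detail left for later.

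**Conclusion.** The point holds in a limited form. The article commits to removing a term that the T1–T2 half of the primary outcome needs, on the result of a test with roughly 16% to 53% power under the assumed inputs. When the group-by-quadratic term goes and the effect is largely complete by T2, the T1–T2 difference is understated and its nominal 95% interval is badly miscalibrated. If the effect comes only at T3, the rule tends to report a T1–T2 effect that is not there. T1–T3 is little affected under a maintained effect, and power is a minor issue.

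The sizes rest on 52 per arm, the T2 and T3 weeks, the correlation range, the shape of the true effect, and the test being on group-by-quadratic. The direction of the T1–T2 error does not depend on the sample size or correlation, only on the shape of the effect.

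**What to change.** Delete the removal clause in {20a}. Replace it with text to this effect: time is categorical (T1, T2, T3) with group-by-time terms, no time terms are removed, and the between-group T1–T2 and T1–T3 contrasts are the reported effects. Always keeping linear and quadratic time with both group interactions is equivalent for the means.

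For outcomes measured only at T1 and T2, state a single group-by-T2 contrast. The within-person covariance structure is a separate choice and need not be settled here. The differing descriptions of T3 timing should be reconciled, because visit spacing drives the size of the error under any straight-line model.

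The cost is about one sentence. With three visits, categorical time uses the same number of mean parameters as linear plus quadratic time. Under the maintained effect the T1–T2 contrast gives up some rejections (72% against 80% at week 12, ρ = 0.5) in return for an unbiased estimate.
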